#### Criteria for discontinuing or modifying allocated interventions {11b}

Adverse events of the NIV interface can be due to both the adaptation of the orofacial mask or the Owner mask, and treatment will be stopped in the case of any events occurring which are considered serious or intolerable in the judgment of the investigators and the data monitoring committee (DSMB) and under medical consent.

Interruption of the experimental treatment will occur by:
Air leakage around the mask with air leak detected in the mechanical ventilator > 24 l/minPatient-mechanical ventilator asynchrony due to the occurrence of leakage around the maskPressure of fixing the mask against the excessive face that may cause the risk of skin ulcerationTraumatic skin injury due to direct contact with the maskSigns of corneal drynessDiscomfort related to the use of the maskPhobia of staying in a closed environment, with signs of intolerance to the adaptation of the maskPsychomotor agitation after adaptation of the maskLevel of 10 mmHg CO_2_ increase from baseline

Individuals who declare they no longer wish to participate at any time or who present criteria for interrupting NIV will be discontinued from the study, according to the recommendations of the *Associação de Medicina Intensiva Brasileira* (*AMIB*) [15].

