Although the significant escape of infectious aerosols is a risk in NIV, it is recommended that aerosolization is minimized by the use of an appropriate interface and the use of filters such as the high-efficiency particulate arrestance (HEPA) in the expiratory branch [9, 10]. It is additionally recommended that all non-invasive treatments should be monitored closely due to the risk of rapid clinical deterioration [6]. According to Landry et al. [11], mask leaking from positive pressure systems may be a major source of environmental contamination and nosocomial spread of infectious respiratory diseases and that improvised diving masks show greater leaking at higher flow rates compared to standard continuous positive airway pressure (CPAP) masks at pressures greater than 10–12 cmH_2_O. Therefore, NIV should be used with CPAP pressure levels of up to 12 cmH_2_O, with the aim of minimizing aerosolization, maintaining peripheral oxygen saturation (SpO_2_) between 93 and ≤ 96%, inspired fraction of oxygen (FiO_2_) ≤ 50% and respiratory rate (RR) < 24 bpm, which should be evaluated within 1 h [11, 12].

Predicting the lack of materials to meet the needs of these patients in the intensive care units (ICU), the “Mergulhadores do Bem” group from the Universidade de Santa Cruz do Sul—RS/Brazil, inspired by the idea implemented in Italy and used in hospitals (https://www.isinnova.it/easy-covid19/), adapted masks used for diving (snorkeling) to be used as NIV masks, called the Owner mask, which can be adapted to traditional mechanical ventilators and portable non-invasive ones (http: //www.mergulhadoresdobem.com.br/).

Thus, in view of the urgent need to develop measures to assist in ventilatory care for patients with SARS-CoV-2 infection, the Owner mask was designed to prioritize protection and assist in respiratory function, allowing an adequate seal on the patient’s face and minimizing the virus aerosolization in the environment. Considering that patients with COVID-19 can benefit from early non-invasive ventilatory strategy and that the interface for NIV needs to avoid aerosolization for the environment to reverse/minimize the acute respiratory failure (RF), the present study aims to assess the safety and efficacy of the Owner mask in relation to the conventional orofacial mask for performing NIV.

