### Trial design {8}

This is a three-phase, parallel group, randomized, non-blinded, controlled, multicentric study guided by outcome. The allocation ratio is 1:1 in favor of the Owner mask to maximize learning about the experimental treatment, while also allowing a wider pool of patients to have access to the experimental treatment in order to support recruitment.

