### Interventions

#### Explanation for the choice of comparators {6b}

The active arm is the use of the Owner mask to implement NIV, in addition to routine supportive care. The Owner mask (Owntec Soluções em Engenharia, Santa Cruz do Sul, Brazil) was chosen for evaluation because there is safety data from the pilot study which proved reduced air leakage due to its better seal on the patient’s face. The control arm is composed of patients who will undergo NIV using the traditionally used orofacial interface.

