**Fig. 1 Fig1:**
[figure not shown]
Flowchart of the study

NIV will be instituted in CPAP or bi-level positive airway pressure (BiPAP) mode with expiratory positive airway pressure (EPAP) and inspiratory positive airway pressure (IPAP) levels of up to 10–12 cmH_2_O. NIV will be used for 30 min to 1 h for patients with COVID-19, with gas analysis before and after this period. Sessions in non-COVID-19 patients can last up to 2 h, and NIV can be used intermittently, as long as there is no clinical worsening or signs of failure [13, 14].
CPAP: hypoxemic respiratory failure, with positive expiratory end pressure (PEEP) between 5 and 12 cmH_2_O and FiO_2_ minimum to maintain SpO_2_ ≥ 94%BIPAP: hypercapnic respiratory failure, start with IPAP necessary to maintain SpO_2_ > 94% and with maximum levels up to 10–12 cmH_2_O. Tidal volume up to a maximum of 9 ml/Kg/predicted weight, EPAP (PEEP) between 6 and 8 cmH_2_O and FiO_2_ minimum enough for SpO_2_ ≥ 94%

NIV will be performed by a conventional mechanical ventilator, preferably by SERVO-S (Maquet Critical Care, São Paulo, Brazil), or by the one available at each research center. The criteria for its interruption will be those of clinical worsening (determined by the medical team) such as the occurrence of hemodynamic instability, depression of the cognitive state, psychomotor agitation, lack of airway defense, lack of adaptation to the interface, and severe bronchospasm [15]. Success or reduction in the severity of RF will be considered by the oxygenation index through the PaO_2_/FiO_2_ > 200, reduction in RR < 30 bpm and SpO_2_ ≥ 94% [12, 16].
NIV Owner group (experimental group)
Patients with suspected or confirmed COVID-19 undergoing NIV with an Owner maskPatients with RF due to causes unrelated to COVID-19 submitted to NIV with Owner maskNIV orofacial group (control group)
Patients with suspected or confirmed COVID-19 undergoing NIV with conventional orofacial maskPatients with RF due to causes unrelated to COVID-19 submitted to NIV with conventional orofacial mask

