#### Relevant concomitant care permitted or prohibited during the trial {11d}

All concomitant care and interventions are permitted other than concomitant receipt of any other experimental treatment. Patients will use the drug therapy indicated by the attending physician. The NIV will be implemented by using a diving mask adapted into a mechanical ventilator, a HEPA filter in the expiratory branch, and a heat and moisture exchanger (HME) filter in the trachea Y, with it being performed twice a day for 60 min., with positive pressure levels of up to 10–12 cmH_2_O whenever there is a clinical indication to do so [12].

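### The stopping list with the 24 l/min leak limit is headed as if it governs the Owner mask only; read literally, it can remove high Owner leak values before the 1-h reading

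*Protocol article*

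**What the plan says.** Section {11b} opens with a judgement-based rule that names both masks: treatment stops for events considered serious or intolerable. It then gives a nine-item list headed "Interruption of the experimental treatment will occur by". Two items are numeric, a ventilator-detected leak above 24 l/min and a CO2 rise of 10 mmHg from baseline. The other seven are asynchrony from leak, excessive fixing pressure, skin injury, corneal dryness, discomfort, phobia and agitation. The section closes by saying that patients "who present criteria for interrupting NIV will be discontinued from the study".

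Two other places show what the heading's term refers to. Trial design {8} says "The allocation ratio is 1:1 in favor of the Owner mask to maximize learning about the experimental treatment". The group list in Intervention description {11a} reads "NIV Owner group (experimental group" and calls the orofacial arm the control group.

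Intervention description {11a} also has interruption criteria for NIV in either arm. They are decided by the medical team and include "psychomotor agitation, lack of airway defense, lack of adaptation to the interface, and severe bronchospasm". They contain no leak or CO2 threshold.

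Air leak 1 h after NIV and the time from start to end of NIV are both secondary outcomes. Ventilatory parameters are to be read after 1 h. Only the data analyst is blinded {17a}.

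**The concern.** With the term used as in {8} and {11a}, Owner is the only mask with a stated leak limit. An orofacial patient with the same leak continues unless the team judges otherwise, and the team knows the mask. If the limit is crossed before 1 h and the patient leaves the study, the 1-h comparison loses its highest values mainly in one arm.

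Leak matters in this trial. The choice of comparators {6b} justifies the Owner mask by "the pilot study which proved reduced air leakage due to its better seal", while the background {6a} reports that "improvised diving masks show greater leaking at higher flow rates compared to standard continuous positive airway pressure (CPAP) masks". Selective loss of high Owner readings would push the comparison towards the first statement and away from the second. NIV duration would also be cut in Owner by a rule that the other arm lacks, so a difference there could not be read purely as a mask effect.

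**Working it through.** **Step 1: which arm does the list govern?**

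- For Owner only: the heading's term is used for the Owner mask in {8} and matches the group label in {11a}. No list with these limits exists for the orofacial mask.
- For both masks: the section title is plural, the sentence before the list names both masks, and the items say only that it is the mask. The closing paragraph names no arm. Section {11d} uses the term more loosely ("other than concomitant receipt of any other experimental treatment").

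The label points to Owner and the context points to both. The document does not settle it.

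**Step 2: which items create an asymmetry under the literal reading?**

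Agitation and intolerance of the interface are already covered for both arms by {11a}, and serious or intolerable mask events by the opening of {11b}. The explicit one-sided limits are leak and CO2. The CO2 limit matters little, because the scheduled gas that trips it is generally the one that supplies the outcome value. The leak limit carries the point.

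**Step 3: how much could it distort the 1-h leak comparison?**

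The protocol gives no leak distribution or trigger timing, so there is no planned figure to reproduce for leak. The arm sizes used as inputs, 63 and 97 (Sample size {14}), do reproduce from n = [1.96√(2p̄q̄) + 0.842√(p₁q₁ + p₂q₂)]² / (p₁ − p₂)²:

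- 30.2% against 10.2%: (1.113 + 0.463)² / 0.04 = 62.1, so 63.
- 61% against 41%: (1.386 + 0.583)² / 0.04 = 96.9, so 97.

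These sizes are unaffected by this point.

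Assumptions: leak is identical in the two arms; a share p of patients lies above 24 l/min; a fraction f of those Owner readings, and g of those control readings, is lost before 1 h. The test is the planned Mann-Whitney test at 5%. With 6,000 simulated trials per setting, the simulation standard error near 5% is √(0.05 × 0.95 / 6000) = 0.28 percentage points.

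False-positive rate (%), shown for p = 5 / 15 / 30%:

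| Control loss | f | n = 63 per arm | n = 97 per arm |
|---|---|---|---|
| half the Owner rate (g = f/2) | 10% | 4.9 / 5.1 / 4.7 | 5.1 / 4.9 / 5.3 |
| | 25% | 5.4 / 4.9 / 5.6 | 5.0 / 5.6 / 5.7 |
| | 50% | 4.8 / 6.4 / 9.6 | 5.2 / 7.0 / 11.6 |
| | 100% | 5.8 / 11.0 / 31.9 | 6.2 / 14.0 / 46.6 |
| none (g = 0, upper bound) | 10% | 4.5 / 5.0 / 5.0 | 5.0 / 5.0 / 5.2 |
| | 25% | 5.1 / 5.7 / 8.2 | 5.1 / 6.9 / 10.5 |
| | 50% | 5.8 / 9.8 / 20.7 | 6.0 / 13.5 / 30.0 |
| | 100% | 7.7 / 29.4 / 78.6 | 9.2 / 41.6 / 92.3 |

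With the same loss in both arms (g = f, at 50% or 100%), the rate is 4.2 to 5.4% for every p and n.

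The mechanism shows in the share above the limit among patients actually read, p(1 − f)/(1 − pf). At p = 15%:

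- Owner, f = 50%: 0.075/0.925 = 8.1%.
- Controls losing at half that rate, 25%: 0.1125/0.9625 = 11.7%.
- Controls losing none: 15%.

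**Step 4: NIV duration.**

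No figure can be given. Sessions run 30 min to 1 h in COVID patients and up to 2 h, possibly intermittently, in others {11a}. Section {11d} speaks of 60 min twice a day. The outcome list does not say whether duration means one session or the whole course.

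**The case against.** The strongest reply is that a one-sided rule is inferred from one word, while most of {11b} reads as applying to both masks. That is fair. A reader might infer that the sponsor meant to stop only Owner patients on leak, and the document does not establish this. What stands is that the heading, in the protocol's own vocabulary, names one arm, and the staff who follow it know the arm.

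It is also fair that seven of the nine items need clinical judgement and partly overlap with criteria covering both arms. A contrast of numeric limits in one arm with pure judgement in the other would overstate the difference, which rests essentially on the leak item.

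A tighter limit for an adapted diving mask could be defended on safety grounds, given the leak evidence in {6a}. But {11b} gives no reason for confining it to one mask, and a common limit protects Owner patients equally.

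Finally, loss of readings is assumed. Data collection {18a} registers data of discontinued subjects, and intention-to-treat is planned {20a, 20c}. Neither says that the leak at interruption stands in for the 1-h value, but the full protocol or analysis plan may. That silence is therefore not counted as a fault here. It does mean that the loss is possible, not certain.

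**Conclusion.** The heading needs correcting. As worded, the leak limit is explicit for Owner only, and combined with discontinuation from the study it can bias the 1-h leak comparison in favour of Owner and make NIV duration differ partly by rule. That the term is attached to Owner elsewhere is plain; whether a one-arm rule was intended is open.

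The size is unknown. All of p, f and g are assumptions. With a quarter or fewer of the high Owner readings lost and controls losing half as many, the error rate stays at about 5 to 6%. It becomes material only when many Owner patients exceed the limit and most of those readings are lost. The rates near 79% and 92% need 30% above the limit, every such Owner reading lost and no control reading lost. A reader should not take them as expected, since the criteria for both arms would also stop some poorly fitting orofacial masks.

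A reader might also infer a biased intubation comparison. The asymmetry does not support that: removal of interrupted patients from the study is a separate matter that arises however the heading is read.

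**What to change.** Reword the heading in {11b} so that the list governs interruption of NIV with either mask. In both arms, record the leak value and the trigger met at interruption, and use that leak value in the leak comparison when NIV stops before 1 h. For interrupted patients, replace discontinuation from the study with stopping the mask while follow-up continues for intubation and the other outcomes.

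This resolves the ambiguity whichever reading was intended and loses no protection for Owner patients. It costs wording in one section and two CRF fields; leak is already read from the ventilator. The sample size does not change.

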### Outcomes {12}

#### Primary outcome measure

OTI rate in patients with or without suspicion or confirmation of SARS-CoV-2 infection submitted to NIV with Owner mask or conventional orofacial mask.

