### Data collection and management

#### Plans for assessment and collection of outcomes {18a}

The data of each research subject (including discontinued subjects) will be registered in the database quickly, completely, and accurately through an electronic form made available to each researcher in their respective hospital and mandatory to be completed and checked by the researchers investigated by the study in each hospital institution. The data administrator will review and modify the data according to the check of the researchers where the research is being carried out.

Analysis of clinical, sociodemographic data, age, sex, and body mass index (BMI) will be performed. An analog pain assessment will subsequently be performed using the VAS [21] and the perception of effort using the Modified Borg Scale. Clinical severity will be quantified using the Simplified Acute Physiological Score III (SAPS III) based on data obtained from the patient’s medical record. The presence of comorbidities, smoking, symptoms, confirmation of SARS-CoV-2 infection, origin of the patient, history of exposure, and complications that may occur during hospitalization will be recorded. The OTI rate will be obtained in patients who have undergone NIV, as well as in-hospital mortality within a period of up to 30 days.

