### Statistical methods

#### Statistical methods for primary and secondary outcomes {20a}

The SPSS software program (version 25.0, IBM, Armonk, NY, USA) will be used for data analysis using the Generalized Estimation Equations (GEE) model. The normality of the data will be assessed using the Kolmogorov-Smirnov test. Identity function, unstructured work correlation matrix, and covariance matrix of the robust estimator will be used using the Bonferroni post hoc test when significant. The chi-squared test will be used to compare the proportions of categorical variables studied in the groups and the Mann-Whitney *U* test to compare the distributions of continuous variables between groups (*p* < 0.05). Analysis by intention-to-treat will be performed to include patients who did not allow analysis of outcomes.

The effect size will be estimated according to Cohen [28], who suggested a cutoff value greater than or equal to 0.8 representing a large effect size, between 0.8 and 0.2 as a medium effect size, and values below 0.2 as a small effect size. The same will be calculated using the variation obtained before and after the intervention, as well as for the post-intervention moment between the groups analyzed. The effect size will be calculated using [name] Effect Size Calculator [http://www.uccs.edu/lbecker/].

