#### Methods in analysis to handle protocol non-adherence and any statistical methods to handle missing data {20c}

The primary analysis will use the intention-to-treat principle and a per protocol analysis will be undertaken to assess the robustness of the findings.

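### Meeting an NIV-interruption criterion ends study participation as written, which conflicts with the intention-to-treat primary analysis and leaves unclear whether intubation is still recorded

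*Protocol article*

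**What the plan says.** **Leaving the study.** Protocol article, Criteria for discontinuing or modifying allocated interventions {11b}: patients "who present criteria for interrupting NIV will be discontinued from the study". The same sentence applies the same consequence to people who no longer wish to take part.

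**The criteria.** Intervention description {11a}, text under Fig. 1: "The criteria for its interruption will be those of clinical worsening (determined by the medical team) such as the occurrence of hemodynamic instability". The list goes on to depressed cognition, agitation, loss of airway defence, failure to adapt to the interface and severe bronchospasm. Section {11b} adds a mask-related list (leak, asynchrony, skin injury, corneal dryness, discomfort, phobia, agitation, CO2 rise), headed "Interruption of the experimental treatment will occur by", although the section opens by naming both masks.

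**Outcome and analysis.** The primary outcome {12} is "OTI rate in patients with or without suspicion or confirmation of SARS-CoV-2 infection submitted to NIV with Owner mask or conventional orofacial mask". Section {20c}: "The primary analysis will use the intention-to-treat principle and a per protocol analysis will be undertaken to assess the robustness of the findings". Section {20a}: "Analysis by intention-to-treat will be performed to include patients who did not allow analysis of outcomes".

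**Data collection.** Section {18a} says that data of every subject, discontinued subjects included, are registered. It then says "The OTI rate will be obtained in patients who have undergone NIV".

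**The concern.** Stopping a treatment and leaving a trial are different events, and intention-to-treat depends on keeping them apart. Section {11b} gives both the same consequence. The clinical-worsening criteria make this serious: Background and rationale {6a} says that intubation becomes the priority once NIV fails. A patient who meets such a criterion is therefore a plausible candidate for the primary event. If follow-up stops there, the missing outcomes are concentrated among patients about to be intubated, and the observed OTI rate is too low.

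Two things could follow. With similar loss in both arms, the trial loses events and power. With unequal loss, the comparison is biased. Unequal loss is possible because the trial is open-label ({8}; only the analyst is blinded, {17a}), several criteria are matters of judgement, and the mask-related list is headed as if it applied to one arm.

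**Working it through.** **Inputs from Sample size {14}:** control OTI 30.2% (COVID) and 61% (non-COVID); absolute reduction 20 points; two-sided alpha 0.05; power 80%; 63 and 97 per group; 20% loss to follow-up. The documents give no rate of NIV interruption and no OTI risk after it. Those values are assumptions below.

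**1. The plan's own figures.** For two proportions with pooled variance and no continuity correction:

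n = [1.96·√(2·p̄(1−p̄)) + 0.8416·√(p1(1−p1) + p2(1−p2))]² / (p1−p2)²

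- COVID, 30.2% v 10.2%, p̄ = 0.202: (1.1129 + 0.4628)² / 0.04 = 62.1, so 63 per group; power 80.6%.
- Non-COVID, 61% v 41%, p̄ = 0.51: (1.3856 + 0.5830)² / 0.04 = 96.9, so 97 per group; power 80.0%.

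Both stated sizes are reproduced.

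**2. Equal loss in both arms.** Suppose a share q of would-be intubated patients leaves before OTI is recorded, with no other loss. The observed rate is p(1−q)/(1−pq), and n(1−pq) patients remain. Example, COVID control, q = 0.25: 0.302·0.75 / (1 − 0.0755) = 0.2265/0.9245 = 24.5%, with 63·0.9245 = 58.2 patients left.

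Power = Φ[(d − 1.96·SE0)/SE1], where d is the observed difference and SE0 and SE1 are the pooled and unpooled standard errors in the remaining patients.

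| q | COVID, observed | Power | Non-COVID, observed | Power |
|---|---|---|---|---|
| 0 | 30.2% v 10.2% | 80.6% | 61% v 41% | 80.0% |
| 25% | 24.5% v 7.9% | 70% | 54.0% v 34.3% | 74% |
| 50% | 17.8% v 5.4% | 55% | 43.9% v 25.8% | 63% |
| 75% | 9.8% v 2.8% | 34% | 28.1% v 14.8% | 43% |

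If the masks are truly equal, both arms shrink by the same formula and the observed difference stays at zero.

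**3. Loss in the Owner arm only, masks truly equal.** If a fraction f leaves with OTI risk r, the observed Owner rate is (p − f·r)/(1 − f).

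- p = 0.302, f = 0.2, r = 0.6: (0.302 − 0.12)/0.8 = 22.75%, a false reduction of 7.45 points.
- p = 0.302, f = 0.2, r = 0.8: (0.302 − 0.16)/0.8 = 17.75%, or 12.45 points.
- p = 0.302, f = 0.1, r = 0.6 or 0.8: 26.9% or 24.7%, or 3.3 or 5.5 points.
- p = 0.61, f = 0.2, r = 0.8: (0.61 − 0.16)/0.8 = 56.25%, or 4.75 points.

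Put in the terms of step 2, with q applied to Owner only, the false reduction in COVID patients is 5.7, 12.4 or 20.4 points for q = 25%, 50% or 75%. The chance of a significant result favouring Owner is then about 10%, 34% or 76%, against a nominal 2.5%.

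**4. OTI recorded for everyone.** None of these losses occurs. The 63 and 97 per group stand, with power 80.6% and 80.0%.

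**The case against.** The strongest reply is that the article can be read as stopping treatment while keeping the data. The heading of {11b} concerns allocated interventions, {18a} requires complete registration that covers discontinued subjects, and {20c} keeps intention-to-treat primary with per-protocol as a check. This stands in part. It means that removal of these patients from the analysis is not established, although a reader might infer it. It does not settle the point: registering a discontinued patient's data does not say that intubation occurring afterwards is ascertained, and {11b} says that the patient leaves the study.

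Other stronger readings also lack support:

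- **That {18a} drops these patients by restricting OTI to those who have undergone NIV.** A patient whose NIV is interrupted has undergone NIV. The phrase could exclude only patients randomised but never started.
- **That the 20% loss allowance comes from this rule.** Section {14} gives no reason for the allowance.
- **That bias must favour Owner.** The sentence that removes patients is neutral as to arm, and the {11a} criteria apply to NIV with either mask. One-arm loss is a possibility raised by the list's heading and the open-label design.
- **That everyone stopped is close to intubation.** This fits the clinical-worsening criteria. It fits corneal dryness, skin injury or discomfort much less well.

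How missing outcomes are handled in the analysis may properly be left to an analysis plan that is not shown, and is not part of this point.

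**Conclusion.** The point holds as a conflict between stated rules. As written, {11b} ends study participation on criteria closely tied to the primary outcome, while {20c} promises intention-to-treat, and no section secures ascertainment of OTI after discontinuation.

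The size and direction of any effect are unknown. The power losses rest on an assumed 25% to 75% loss of would-be intubated patients. The false reductions of about 7.5 and 12.5 points, against a 20-point target, rest on loss confined to one arm, 20% leaving, and an assumed OTI risk of 60% or 80% among them. If sites do record OTI after discontinuation, both effects are nil. The text should secure that, because the primary comparison depends on it.

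**What to change.** Leave the clinical stopping criteria unchanged. In {11b}, replace the wording about leaving the study with a statement that interruption of NIV does not end study follow-up. State that OTI, in-hospital death and length of stay continue to be collected from the hospital record for all randomised patients, who are analysed in their allocated arm, unless consent for data use is withdrawn. Bring {18a}, {20a} and {20c} into line:

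- {18a} should say that outcomes after discontinuation are ascertained.
- {20a} and {20c} should describe the same intention-to-treat set, and the {20a} sentence quoted above should be rewritten to match.

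The statements in {11b} on whether the mask-related list applies to one mask or both must also be reconciled.

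The cost is an amendment to the wording, which {25} routes through the ethics committee. The outcomes come from the hospital record, so no visits are added and no sample-size figure changes.
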